### Data analysis

#### Quantitative

The results of questionnaires completed on behalf of the aged-care staff, participants and family members will be analysed using IBM SPSS Statistics version 25 software (IBM, Armonk, NY, USA). The responses from the aged-care staff will be the main responses considered for analysis. Where available, participants and family responses will be included for secondary analysis. To examine group differences, the participants will be categorised according to their treatment cycle group allocation (group A or group B). Descriptive statistics will be derived. Each variable will be tested for normality. For those variables that meet the normality assumption, two-sided paired and/or independent *t* tests will be used to examine group differences within and between groups. If the normality assumption is violated, then non-parametric tests such as the Wilcoxon signed-rank test will be used. Within-subject differences of the four measurements between the first and second washout periods will be tested using paired *t* tests to ensure that the washout phase is long enough to rule out any carryover effects [51, 52]. All data collection points will be examined using general linear mixed modelling techniques to see if any changes in behaviour, QOL or pain have occurred over the duration of both treatment cycles. The covariates of weight, average dose of medication, and baseline measures will be controlled for in each model, and any interactions will be tested and reported. The proportion of adverse events during the CBM and placebo phases will be tested and reported for each individual. NPI-NH is the primary outcome measure for this study. All other measures (CMAI, QOL-AD, and Abbey Pain Scale) have been included for secondary analysis. The CMAI will be analysed using the reliability change methodology compared with the NPI-NH to allow small changes to be reported [53]. The α-value will be set at 0.05. In the instance where a participant withdraws halfway through a treatment cycle, the information collected prior to withdrawal will be retained in the study because their personal information will have been de-identified. The data management of the information collected will follow standard university procedures, be stored in a locked cabinet for a period of 15 years, be stored on a password-protected computer, and be backed up regularly in a secure format.

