### Participants and setting

Participants will be recruited through residential aged-care facilities. Residential aged-care facilities within Australia are government-funded organisations that provide additional support for families who may have a family member with dementia, whereby many move from their residential homes into a residential aged-care facility so that they can be monitored and provided with additional care. PASS^2019^ power analysis and sample size software (ncss.com/software/pass; NCSS, Kaysville, UT, USA) was used to derive the sample size. The Neuropsychiatric Inventory Questionnaire–Nursing Homes (NPI-NH) is the primary outcome measure. Total sample size for a 2 × 2 crossover design assuming a two-sided *t* test to detect a mean difference of 6 on the NPI-NH scale with a standard deviation of 13 (for the difference) is 40 for a power of 80% and significance level of 5%. Fifty participants will be recruited to allow for a 20% attrition rate. Participants will be eligible to participate if they live in a residential aged-care facility, are aged 65 years or older, have a diagnosis of mild dementia (indicated by a score ≥ 20 on the Mini Mental State Examination [MMSE]), are able to speak English, are known as compliant with taking medication, are not bedridden, and are able to provide informed consent. Participants will be excluded if they have certain health conditions, such as frontotemporal or Lewy body dementia; have other comorbidities, such as epilepsy, anorexia nervosa, comorbid psychiatric conditions, Parkinson’s disease, or congestive heart failure; have a history of myocardial infarction or anginal pain, stroke, liver disease, or renal disease; or are taking medications such as primidone, phenobarbital, carbamazepine, rifampicin, rifabutin, troglitazone, *Hypericum perforatum*, and valproic acid that may interact with cannabis metabolism.

The pre-/post-surveys and focus group discussions are an exploratory, qualitative component of this study, and thus a definitive sample size calculation cannot be determined at this stage. We estimate that six focus groups comprising six to eight participants, including two groups of residential care staff, activity staff (care staff who monitor daily activities and social engagement), and family members, will ensure that data saturation has been reached. Written informed consent will be obtained from all participants, including the residential aged-care staff and the next of kin.

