### Data collection

The aged-care staff, resident participants with dementia, and nominated next of kin will complete a total of four outcome measures on seven occasions throughout the study. The questionnaires take approximately 20 min to complete and will be completed three times during the first treatment arm (baseline [day 0], after maximum tolerated dose has been reached [day 24], and the end of the treatment cycle [day 42]), three times during the second treatment arm (baseline [day 56], after maximum tolerated dose has been reached [day 80], and the end of the treatment cycle [day 97]) and once following the 2-week washout period after the second treatment arm (day 112). The questionnaires will be administered by the primary researcher.

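### The protocol fixes no single CBM-versus-placebo crossover test on NPI-NH, so the 80% power behind its sample size is not secured

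*Protocol article*

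**What the plan says.** The sample size paragraph (Protocol article, Participants and setting) rests on one contrast, from a 2 × 2 crossover analysed by a two-sided t test. Its aim is "to detect a mean difference of 6 on the NPI-NH scale with a standard deviation of 13 (for the difference) is 40". The power is set at 80% and the level at 5%. NPI-NH is the primary outcome, and 50 are recruited to allow for 20% attrition.

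The analysis section (Data analysis, Quantitative) is organised differently: "To examine group differences, the participants will be categorised according to their treatment cycle group allocation (group A or group B"). If the data pass a normality check, paired t tests, independent t tests or both are planned; these "tests will be used to examine group differences within and between groups". If the check fails, non-parametric tests replace them. A general linear mixed model across all visits is also planned. Its stated purpose is to see whether outcomes changed over the two cycles, and it controls for weight, average dose and baseline.

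The Eligibility period section shows that A and B are the randomised groups that fix which treatment comes first. The Randomisation section nevertheless calls them the placebo group and the treatment group, although everyone receives both.

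The Data collection section puts the second cycle's baseline on day 56 and its last assessment at "the end of the treatment cycle [day 97"]. The middle assessment of the first cycle is placed "after maximum tolerated dose has been reached [day 24"].

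**The concern.** In a 2 × 2 crossover the treatment effect is the within-person difference between cycles, combined over both orders so that period cancels. Tests organised by order can miss it in two ways. Within one order, everyone takes CBM in the same period, so CBM minus placebo equals treatment plus period drift. Between orders, comparing raw scores in one period turns the trial into a small parallel-group study and gives up the within-person comparison that the sample size depends on.

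Drift is a realistic worry: the Discussion itself expects cognitive decline to progress irreversibly. With several admissible tests and a data-driven switch between parametric and rank methods, the primary result could come from a confounded or underpowered test, or be chosen from several after unblinding.

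**Working it through.** **Inputs.** From Participants and setting: difference δ = 6, SD of the within-person difference 13, N = 40, 80% power, two-sided 5%. From Randomisation: 1:1 allocation, 25 per order, hence 20 per order after 20% attrition. Not in the document, so assumed over a range: the correlation ρ between a person's scores in the two periods (0 to 0.9), and the mean period drift (1 to 6 points).

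**1. The plan's own figure.** Noncentral t for the crossover contrast: noncentrality = 6 / (13/√40) = 2.92, with 40 − 2 = 38 degrees of freedom. Power is 81.2%. N = 39 gives 80.1%, and rounding to equal orders gives 40. Attrition: 40 / (1 − 0.20) = 50. The stated numbers reproduce.

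**2. Paired test inside one order.** With n = 20, noncentrality = 6 / (13/√20) = 2.06 on 19 degrees of freedom, giving 50.0% power.

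The same formula with the drift in place of δ gives the rejection rate when the drug does nothing:

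| Assumed period drift (points) | Rejections with no drug effect |
|---|---|
| 1 | 6% |
| 2 | 10% |
| 3 | 17% |
| 4 | 26% |
| 6 | 50% |

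**3. A against B on scores in one period.** A single score has SD = 13 / √(2(1 − ρ)). With 20 per group, noncentrality = 6 / (SD × √(2/20)) on 38 degrees of freedom.

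| Assumed ρ | SD of one score | Power |
|---|---|---|
| 0 | 9.2 | 52% |
| 0.3 | 11.0 | 39% |
| 0.5 | 13.0 | 30% |
| 0.7 | 16.8 | 20% |
| 0.9 | 29.1 | 10% |

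No value of ρ in this range comes near 80%.

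**4. Readings that do work.** An independent t test of A against B on each person's period 1 minus period 2 difference has 81.2% power. Simulation kept it at about 81% with a period effect of 0, 3 or 6 points. A paired CBM-minus-placebo test over all 40 has about 81% with no period effect, and about 75% at a 6-point period effect with 20 per order.

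**5. Visit days.** The first cycle runs from day 0 to day 42. The second starts on day 56, and 56 + 42 = 98; the final visit confirms this, since 98 + 14 = 112. Day 97 is one day short. In Table 1 an event-free participant first takes the top step at both daily doses on day 23. One 2-day hold moves that to day 25 (23 + 2), after the day 24 visit; day 80 is the same point in the second cycle (56 + 24).

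**The case against.** The strongest reply is that the wording is loose rather than wrong. The standard test for this design is an independent t test between orders on period differences, which requires participants to be sorted by order; a paired test pooled over everyone also fits. Both reach about 81% when there is no period effect. This stands. A reader might infer from the text that the trial will fail to deliver its stated power, but the document does not support that: it leaves the valid tests open alongside the weak ones. Nor does it anywhere propose comparing A with B on scores averaged over both cycles.

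A second reply is that an article need not list every model term, so the absence of treatment, period and sequence from the mixed model is not in itself an error. That also stands. The omission aside, the model cannot be relied on to supply the missing contrast, because its stated purpose is change over time. It also adjusts for average dose, which is set by tolerability after randomisation and can distort the treatment effect.

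Third, the drift and correlation values are assumptions. They are, which is why ranges are shown; the 50% power in step 2 needs neither.

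Finally, one might conclude that day 24 precedes the maximum tolerated dose for anyone ever held back. That is too broad. Under the adverse events section, a participant whose events recur after two attempts stays at the earlier dose, and may have reached their maximum well before day 24. The timing problem concerns those held once who then resume escalation.

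**Conclusion.** The concern holds in a limited form. The sample size is right for the crossover contrast on 40 completers (81.2%), but the analysis section does not commit to that contrast. Two plain readings of what it does state give 50% power with treatment and period confounded, or 52% to 10% depending on the assumed correlation. The stated power is therefore not secured. This is more than missing detail, because the grouping, the family of tests, the normality trigger and the dose adjustment are all stated, and following them literally can yield a confounded or underpowered primary result. The size of any false-positive inflation depends on a drift that the document does not give: from 6% at 1 point to 50% at 6 points for the within-order test.

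The day 97 slip is real but minor; no effect on any estimate has been shown. The day 24 and day 80 labels are also a minor point.

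**What to change.** Before unblinding, name one primary analysis: the CBM-minus-placebo difference in end-of-cycle NPI-NH, with its 95% confidence interval, from a linear mixed model with treatment, period and sequence as fixed effects and participant as random effect. The two-sample t test between orders on period differences is an equivalent choice. Do not adjust this analysis for average dose. Make the rank-based version, a rank-sum test of period differences between orders, a fixed sensitivity analysis rather than one triggered by a normality test. Describe A and B as sequences throughout, including in the Randomisation section.

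Separately, reconcile day 97 with the 6-week cycle that starts on day 56, and describe days 24 and 80 as mid-cycle visits that may fall before the maximum tolerated dose for some participants.

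The cost is wording in the protocol or SAP. The data, sample size and software stay the same.

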**Methods/design:**

We will carry out an 18-week, randomised, double-blind crossover trial that consists of a 2-week eligibility period, two 6-week treatment cycles, and two 2-week washout periods (between both cycles and after the second treatment cycle). We aim to recruit 50 participants with dementia who are living in residential aged-care facilities. The participants will be randomised into two groups and will receive a dose of either CBM oil or placebo for the first treatment cycle and the opposite medication for the second. Data will be collected using the Neuropsychiatric Inventory Questionnaire, the Cohen-Mansfield Agitation Inventory, the Quality of Life in Alzheimer’s Disease questionnaire, and the Abbey Pain Scale on seven occasions. These will be completed by the participants, aged-care staff, and nominated next of kin or family members. The participants’ heart rate and blood pressure will be monitored weekly, and their body composition and weight will be monitored fortnightly by a research nurse, to assess individual dose response and frailty. In addition, pre- and post-surveys will be administered to aged-care staff and family members to understand their perceptions of CBM and to inform proposed focus groups consisting of the aged-care staff and next of kin.

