## Methods and general study design

This study has received approval from the Human Ethics Research Committee at the University of Notre Dame Australia. The study will use a parallel mixed methods design. The research methodology for this study is a phase II, randomised, placebo-controlled crossover trial. The design will include a 2-week eligibility (assessment) period, two 6-week-treatment cycles to allow each participant to take part in both the control and treatment cycles, and two 2-week washout periods (one between both treatment cycles and the other after the second treatment cycle). The 6-week treatment cycles have been selected on the basis of safety, pharmacodynamics, and pharmacokinetics as reported by Ahmed et al. [14], and a 2-week washout period has been shown to be safe and an appropriate length of time for cannabis to metabolise in older individuals [44].

In addition, residential aged-care staff and next of kin perceptions towards the use of CBM oil will be evaluated via surveys administered prior to and upon completion of the study. At the end of the second treatment cycle, the residential aged-care staff and family members will be asked to participate in a follow-up focus group to gather more in-depth information regarding individuals’ perceptions before and after the administration of CBM. Each participant will be in the trial for approximately 4 months (18 weeks), but the duration of the study will last over 12 months in order to recruit participants from a number of aged-care facilities.

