### Randomisation

The randomisation process for this study will be done by creating a random number list using a 1:1 ratio allocation to ensure an equal number of cases in both the placebo group (*n* = 25) and the treatment group (*n* = 25) using Excel software (Microsoft Corp., Redmond, WA, USA). The determination of participant allocation will be completed by the laboratory manager in the drug manufacturing laboratory, with each case being provided a unique identification (ID) number (1–50). The primary researcher, who is responsible for recruitment, will provide the laboratory manager with the participant’s name to be sequentially matched against with the next available ID number. The laboratory will provide the pharmacy with both CBM and placebo in identical bottles labelled with the ID, but the medical practitioner and research team members will not know the order of treatment until the completion of the study. The pharmacist will place the participant’s name on the bottle before distributing the bottles to the aged-care facilities.

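### The planned carryover check (paired t tests of first against second washout) cannot detect carryover, because the effect cancels across the two sequences

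*Protocol article*

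**What the plan says.** The Quantitative part of the Data analysis section fixes the contrast: "Within-subject differences of the four measurements between the first and second washout periods will be tested using paired" (the test named is the t test). It also fixes the purpose, which is given as follows: "to ensure that the washout phase is long enough to rule out any carryover effects". The sentence names no group, sequence term or between-group contrast. Groups A and B appear earlier in the paragraph for a different purpose: "To examine group differences, the participants will be categorised according to their treatment cycle group allocation (group A or group B").

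The features of the design that matter here are:

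- **Treatment order** (Abstract, Methods/design): participants "will receive a dose of either CBM oil or placebo for the first treatment cycle and the opposite medication for the second".
- **Allocation** (Randomisation): 1:1, 25 per group.
- **Washouts** (Methods and general study design): "two 2-week washout periods (one between both treatment cycles and the other after the second treatment cycle").
- **Measurements** (Data collection): the end of the first washout is the second-cycle baseline at day 56, and the end of the second is measured "once following the 2-week washout period after the second treatment arm (day 112").

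**The concern.** A carryover check has to contrast a washout that follows CBM with one that follows placebo. First against second washout is not that contrast. It compares week 8 with week 16, and which of the two follows CBM depends on the participant's sequence. In a balanced crossover the test therefore mainly measures change over time.

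Two errors can follow. Real carryover can pass unnoticed and the washout be reported as adequate. Ordinary drift in a progressive condition can be reported as carryover. The first matters more. Day 56 is also the baseline of the second cycle, and the models are to control for baseline measures, so an undetected residual effect would enter that covariate and could bias the NPI-NH comparison.

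**Working it through.** **Inputs**

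- From the protocol: two sequences, 1:1; washout measurements at days 56 and 112; target difference 6 points on the NPI-NH; SD of the difference 13; two-sided 5% level; 40 evaluable participants out of 50 recruited.
- Assumed: 20 completers per sequence, and SD 13 for the day 56 minus day 112 difference. The protocol gives 13 for the difference in its sample size calculation and gives no SD for the washout difference, so 8 and 18 are shown as well.

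**The plan's own figure.** The standard error with 40 participants is 13/√40 = 2.055. The noncentrality is 6/2.055 = 2.92, and with 38 degrees of freedom power is 0.812. So 40 is adequate, and 40/(1 − 0.2) = 50. Both stated sample sizes reproduce, and this finding does not affect them.

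**Expected value of the planned difference.** Let c be the residual effect of CBM relative to placebo at the end of a washout, and T the mean day 56 minus day 112 difference due to time alone. The sign of c does not matter below.

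| Sequence | Day 56 follows | Day 112 follows | Mean of day 56 − day 112 |
|---|---|---|---|
| CBM first | CBM | placebo | T + c |
| Placebo first | placebo | CBM | T − c |

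With n₁ CBM-first and n₂ placebo-first participants, the mean over the whole sample is T + c(n₁ − n₂)/(n₁ + n₂). With n₁ = n₂ this is T, and c has gone.

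**Rejection rates of the paired test over the whole sample** (simulation, 20 per sequence, T = 0)

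| c (points) | SD 8 | SD 13 | SD 18 |
|---|---|---|---|
| 0 | 5% | 5% | 5% |
| 3 | 4% | 4% | 5% |
| 6 | 2% | 3% | 4% |
| 10 | 0.2% | 1% | 2% |

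Rejection falls as carryover grows. Carryover leaves the mean unchanged and only widens the spread of the differences.

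**The same test with drift and no carryover.** Noncentrality is T/(SD/√40), with 39 degrees of freedom. At SD 13 it rejects in 30%, 48% and 81% of trials for T = 3, 4 and 6. For T = 4 it rejects in 87% at SD 8 and 28% at SD 18.

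**Unequal completers** (SD 13, c = 6, T = 0). With 22 and 18 the rejection rate is about 4%; with 25 and 15 it is about 8%. Little of the signal leaks through.

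**Run within one sequence.** The CBM-first group alone estimates T + c. With c = 6 and T = −6 the mean is zero and the test rejects in 5% of trials, so a full-sized carryover is invisible. With c = 0 and T = 6 it rejects in about 50%.

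**Between-sequence contrast of the same differences.** Its mean is (T + c) − (T − c) = 2c, so T drops out. Half of it estimates c, with standard error ½ × 13 × √(1/20 + 1/20) = 2.055 and 95% half-width 2.024 × 2.055 = 4.2 points (2.6 at SD 8, 5.8 at SD 18). At SD 13, power is about 30% for c = 3, 81% for c = 6 and over 99% for c = 10. Under drift alone it rejects at the nominal 5%.

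**The case against.** **The article does not say the test is pooled.** True. The surrounding text mentions paired and independent tests within and between groups, so a paired test run by sequence is conceivable. Then c does not cancel, but it is confounded with T. The whole-sample reading is the plain one because no group is named, and neither reading isolates carryover.

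**Other analyses might show carryover.** The mixed models use all data collection points, with interactions tested, and a group-by-time term would hold the contrast needed. A between-group test at day 56 would also fit the general wording. Neither is described as a carryover check, so they do not repair the sentence, though it would be too strong to say the data analysis could never reveal carryover.

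**The figures are illustrative.** This stands. The SD is borrowed, no drift of 4 points is documented, participants have mild dementia, and a 6-point carryover means the full target effect persists two weeks after stopping. With no drift, the false-alarm rate is the nominal 5%. The cancellation itself depends on none of these inputs.

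**Nothing in the protocol hangs on the result.** Also correct: no switch of analysis is stated. The direct harm is a misleading assurance about the washout. The replacement is not strong against small carryover either (30% power at 3 points), which is why it should be reported as an interval.

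**Conclusion.** The concern holds. The protocol names a test whose expected value, with equal sequences, contains no carryover term, and gives its purpose as ruling carryover out. That follows from the design alone. Under the assumed 20 per sequence and SD 13, it rejects in about 3% of trials when carryover equals the whole 6-point target and in about 48% when there is only a 4-point drift. Varying the SD from 8 to 18 leaves the first figure between about 2% and 4%; the second moves between 87% and 28%. Separately, non-significance would not establish absence even with a well-chosen contrast. The point concerns the carryover check only; the sample size stands.

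**What to change.** Replace the sentence on the washout comparison with the following:

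1. Estimate carryover as half the difference between sequences (CBM first minus placebo first) in the within-participant day 56 minus day 112 change. This averages the residual effect over the two washouts.
2. Also estimate the CBM-first versus placebo-first difference at day 56, adjusted for the day 0 value.
3. Report both with 95% confidence intervals for each of the four measures, and judge washout adequacy from the intervals.
4. Remove the claim that a test result can rule out carryover, and state that the result will not be used to change the primary analysis.

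The cost is a wording change in the protocol and analysis plan. Days 0, 56 and 112 are already scheduled for all four measures, so no visit, participant or measurement is added. The change should be made before unblinding.

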#### Experimental phase

This phase of the study will take 16 weeks to complete. To minimise the risk of adverse events and variation in the maximum tolerated dose of CBM oil, each participant will receive one dose on the first and second days (2 pm) and two doses (9 am and 2 pm) for the reminder of both treatment cycles. A registered nurse will administer the dose along with a small meal (e.g., morning and afternoon tea), and the rate of titration will be monitored by the pharmacist to ensure it is appropriate for each individual. The participant will gradually receive an increased dose (titration) of the medication over several weeks, as shown in Table 1. During these weeks, the participant along with the care staff will record the presence of, and any change in, any potential adverse events that may be associated with the medication after the first dose, each afternoon when the dose is increased, and again on the final day of medication. If an adverse event is noted, the participant will revert to their previous best tolerated dose using the adverse events and safety protocol listed below.

**Table 1 Tab1:** Titration administration, including dose and number of sprays

Day(s)	Week	Dose administered (daily)		Number of spray(s) per dose	Adverse events recorded (time)
		9 am	2 pm		
**1**, 2	1	–	**2.5 m**g	1	3 pm
**3**, 4	1	2.5	2.5	1	
**5**, 6	1	2.5	**5**	1–2	3 pm
**7**, 8	1	5	5	2	
**9**, 10	2	5	**10**	2–4	3 pm
**11**, 12	2	10	10	4	
**13**, 14	2	10	**15**	4–6	3 pm
**15**, 16	2/3	15	15	6	
**17**, 18	3	15	**20**	6–8	3 pm
**19**, 20	3	20	20	8	
**21**, 22	3/4	20	**25**	8–10	3 pm
**23**, 24	4	25	25	10	3 pm

Adverse events will be recorded 1 h after drug administration on days of dose increase (days bolded) and on the last day of the treatment period

An upper limit of 50 mg/day of THC will be permitted in those who do not experience any adverse events from the medication. Once a participant has reached their maximum tolerated dose (or a total of 50 mg/daily of THC), they will continue to receive that dose until the cessation of the 6-week period. The placebo group will follow a similar titration process using the indicated volumes shown in Table 1. They will continue to receive an increase in the volume of medication until they record an onset of an adverse event, at which time they will continue to take that volume of placebo until the end of the 6-week placebo cycle.

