### Adverse events and safety protocol

An adverse events protocol will be put into place to minimise any potential harm or risks of receiving additional medication [14]. This will include participants reporting if they have experienced any adverse events 1 h after the increased dose has been administered (*see* Appendix). If moderate to severe adverse events are recorded (determined as ‘Somewhat worse’ (moderate) or ‘Much worse’ (severe) on the participant’s adverse event record) and these events have not ameliorated by the time for the next dose, the participant will receive the previous best tolerated dose. If the effects of the adverse event(s) have disappeared or become milder and do not interfere with the participant’s daily functioning or well-being, the registered nurse may increase the dose at the indicated rate. Recurrence of adverse events after two attempts to increase the dose will result in the participants remaining at their previous best tolerated dose for the remainder of the intervention period. A participant who experiences an adverse event will stay on the previous dose for another 2 days before the next dose is increased. At the beginning of the titration phase, a staff member at the aged-care facility will be vigilant in monitoring any acute adverse events such as dizziness, discoordination with a danger of falls and injury, and extreme fatigue. Any adverse events recorded will be reported to a facility line manager and will then be communicated to staff during shift changes.

Additional safety monitoring will be completed by a research nurse who will meet with each participant to discuss their adverse event records and measure their heart rate and blood pressure twice per week. In addition, the participant’s weight and non-invasive body composition measures such as lean body mass, bone mass, body fat percentage, and fat mass will be measured once per week using a portable scale. In addition, a nurse-led review will be completed 2 days into the washout periods to monitor the participant’s withdrawal symptoms once no more medication is being administered.

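### The mixed models adjust for average dose, which adverse events set after randomisation, so their CBM-versus-placebo coefficient would not estimate the randomised effect

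*Protocol article*

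**What the plan says.** The Quantitative part of Data analysis plans two kinds of comparison.

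- Unadjusted tests: paired and/or independent t "tests will be used to examine group differences within and between groups", with Wilcoxon-type tests if normality fails.
- Mixed models: "All data collection points will be examined using general linear mixed modelling techniques". For these, "The covariates of weight, average dose of medication, and baseline measures will be controlled for in each model", and interactions are to be tested.

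NPI-NH is named as the primary outcome. Neither kind of analysis is named as primary.

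The Experimental phase section describes how dose arises. "An upper limit of 50 mg/day of THC will be permitted in those who do not experience any adverse events from the medication"; otherwise, "If an adverse event is noted, the participant will revert to their previous best tolerated dose". Then, "Once a participant has reached their maximum tolerated dose (or a total of 50 mg/daily of THC), they will continue to receive that dose" to the end of the six-week cycle. On the control side, "The placebo group will follow a similar titration process using the indicated volumes shown in Table 1", and the volume likewise stops rising at an adverse event. The section on adverse events and safety adds rules for holding a dose and for repeat attempts to raise it.

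Weight is recorded with the baseline information (Eligibility period). It is also among the body measures that "will be measured once per week using a portable scale" (Adverse events and safety protocol).

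**The concern.** A covariate in a treatment comparison should not itself be a consequence of treatment. Average dose is one: it records how far each participant could be titrated before adverse events intervened.

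It also shares content with the outcome. The adverse event record in the Appendix lists anxiety, depression and euphoria, which belong to the first ten NPI-NH domains, and sleep and appetite, which enter the 12-domain score. A participant who becomes anxious on treatment may therefore have both a lower dose and a higher NPI-NH score.

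Holding dose fixed changes the question from the effect of being assigned to CBM to a contrast at equal achieved dose, which randomisation does not protect. Depending on coding, the result could be a very imprecise coefficient, one near zero for a drug that works, or one biased in either direction. This is a stated rule rather than a detail left to an analysis plan.

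**Working it through.** **1. The plan's own figure.** Inputs from Participants and setting: difference 6, SD of the difference 13, two-sided 5%, power 80%. The normal approximation gives ((1.960 + 0.842) × 13/6)² = 36.8. The noncentral t gives 80.2% power at 39 and 81.2% at 40. Rounding 39 up to an even number gives 40, and 40/0.8 = 50. The stated 40 and 50 reproduce, and rest on a t test with no covariates. The unadjusted SE is 13/√40 = 2.06.

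**2. What average dose can be.** Table 1 gives two days at each daily total of 2.5, 5, 7.5, 10, 15, 20, 25, 30, 35, 40, 45 and 50 mg THC, which sum to 570 mg over 24 days. The remaining 18 days at 50 mg add 900 mg. The total is 1,470 mg, and 1,470/42 = 35.0 mg/day, the most a cycle average can be. A participant held at 20 mg/day averages (120 + 30 × 20)/42 = 17.1; one held at 2.5 mg/day averages 2.5.

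**3. Coding as THC mg per period, placebo = 0.** The dose difference within a participant is then the CBM average, with mean m and SD s. Regress the CBM-minus-placebo outcome difference on that dose. The treatment effect is the intercept, the predicted difference at zero dose, and:

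- SE(adjusted) = 2.06 × √(1 + (m/s)²)
- correlation of dose with treatment = 1/√(1 + 2(s/m)²)

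Both depend only on m/s, which the article does not give. Two assumed values:

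| m/s | Correlation | SE | Power for a true effect of −6 |
|---|---|---|---|
| 2.2 | 0.84 | 5.0 | about 22% |
| 5.5 | 0.97 | 11.5 | about 8% |

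Simulated crossovers (N = 40, 1,500 runs per scenario, Table 1 averages, assumed distributions of tolerated dose) agree: correlation 0.84 to 0.97, SE 5.0 to 11.6, power 8-23%, against about 80% unadjusted.

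If the true effect is −6 × dose/m, the dose slope absorbs all of it. The intercept is then 0 and rejects about 5% of the time. If tolerated dose also correlates 0.3 with the period's NPI-NH residual (assumed), the coefficient shifts by about +6 to +14 points, and type I error under no effect is about 23%.

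Under this coding treatment × dose equals dose, so that interaction cannot be tested.

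**4. Coding as volume in both periods.** Simulation with the same N and SD:

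| Tolerability | Residual correlation | Dose-treatment correlation | Adjusted estimate (true −6, constant) | Result |
|---|---|---|---|---|
| Equal | 0 | about 0 | −6.0 | SE 2.05, power about 80% |
| CBM lower | 0 | −0.68 | unbiased | SE about 3.4, power about 39% |
| CBM lower | 0.3 | −0.68 | −10.6 | type I error about 31% under no effect |

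With CBM tolerated less well, no residual correlation and an effect proportional to dose, the estimate is −9.0 instead of −6.

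**5. One average dose per participant, used in both periods.** The covariate is constant within a participant and drops out of the within-participant contrast. Adjusted and unadjusted results were identical in simulation.

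**The case against.** The strongest reply is that the article plans more than the mixed models. The t and Wilcoxon tests carry no covariates, and the sample size was built on a t test. The mixed models are described as looking for change over the two cycles, with no treatment term spelled out. This stands: the damage is confined to the mixed models. A reader might infer that the trial's headline NPI-NH result would be the dose-adjusted coefficient, so that an effective drug would be reported as null. The article supports neither that nor the opposite, because it names no primary analysis and gives no rule if the two disagree.

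A reader might also infer that dose nearly duplicates the treatment indicator. That holds only with placebo coded as 0 mg THC. The Experimental phase section gives the CBM limit in mg and describes placebo by volume, which makes that coding plausible. But the covariate is called dose of medication, not THC, and the placebo volume is also spoken of as medication. The coding may be settled in a plan that is not shown.

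The same caution applies to weight. A reader might infer that on-treatment weight is the covariate, since weight is measured during treatment and the Background says THC stimulates appetite. The article also lists weight as baseline information and does not say which value enters the models. Baseline weight is a legitimate covariate.

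What the reply does not do is make average dose a valid adjustment. Two codings happen to be harmless (volume with equal tolerability, and one dose per participant), but the article commits to neither. It also gives no ground for assuming that a psychoactive drug titrated to adverse events is tolerated as well as placebo.

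**Conclusion.** The point holds for the mixed models. The article fixes a post-randomisation variable, driven by adverse events that overlap with NPI-NH domains, as a covariate in each of them. A CBM-versus-placebo coefficient from those models does not estimate the randomised effect.

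The size is conditional. It runs from no loss, under participant-level coding or volume coding with equal tolerability, to power of about 8-23% or a coefficient of about 0 under mg coding with placebo at 0. Volume coding with CBM tolerated less well lies between these for power, and can also bias the estimate. The figures rest on the protocol's difference of 6, SD of 13 and 40 evaluable participants, on cycle averages of at most 35.0 mg/day from Table 1, and on assumed dose distributions and an assumed residual correlation of 0 or 0.3.

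The document does not support saying that the trial's main result is necessarily lost, that dose duplicates treatment under every coding, or that on-treatment weight will be used.

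**What to change.** Remove average dose from every model that estimates CBM versus placebo. Use only baseline (day-0) weight and baseline scores as covariates, and say so explicitly. Report dose-response within the CBM cycle separately, labelled exploratory and non-randomised. State whether the unadjusted test or the mixed model prevails for NPI-NH.

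This takes a sentence or two in the protocol or analysis plan, to be settled before unblinding. It changes no dosing, no data collection and no sample size.
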